## Methods

### Study Design

A mixed methods pilot trial was designed as a single-arm open-label study. Informal caregivers will participate in a participatory process of developing, testing, and validating a technological platform to improve their QoL, impact of care, occupational balance, self-management of health, and empowerment.

The 3-month intervention will be based on the use of the TechQoL4Carers technology platform, called *CuidaconTIC* [34], and the Xiaomi Smart Band 7 wearable wristband. Formal assessments using standardized tools will be conducted as follows: baseline (preintervention: t_0_), mid-intervention (at 6 wk: t_2_), and postintervention (t_4_).

Throughout the intervention (t_1_ to t_3_), continuous information will be obtained through data from the platform and the Xiaomi wearable wristband. A qualitative evaluation will be conducted to gain in-depth knowledge about participants’ perspectives on the intervention and study procedures (t_4_).

The trial has been registered on ClinicalTrials.gov with the identification number NCT06226285 [35]. As this is research with people, in this case, caregivers, a favorable report has been previously obtained from the Ethics Committee for Research and Teaching of the Universidade da Coruña (code: 2023_019).

In addition, the SPIRIT (Standard Protocol Items: Recommendations for Interventional Trials) statement [36] and the CONSORT-EHEALTH (Consolidated Standards of Reporting Trials of Electronic and Mobile Health Applications and Online Telehealth) guidelines [37] were adopted for the protocol design. A summary of the trial, based on the World Health Organization (WHO) Trial Registration Data Set [38], can be found in Multimedia Appendix 1.

### Participants, Recruitment, and Eligibility Criteria

The participants in this study will be caregivers of people with disabilities or older people. The sample will be recruited through direct care centers for people with disabilities and older people.

Depending on the functioning of the entities, a meeting will be held in the centers, individually or in groups, with the persons preselected by the centers and the research team to provide detailed information on the project and possible participation. In this meeting, the inclusion and exclusion criteria will be explained and a paper information sheet will be distributed.

Individuals may express their interest in participating through the e-mails included in the information sheet or through the reference persons in each entity. Subsequently, an individual meeting will be held with the candidates to clarify any doubts and, if applicable, to confirm participation in the project by signing the informed consent form.

Informal caregivers will be included in the study if they are 18 years of age or older; perform the role of informal caregiver, are the main caregiver; are living with the person receiving the care; regularly use a smartphone; and commit themselves to wearing an activity wristband regularly during the project. The exclusion criteria were those who had been an informal caregiver for less than 1 year, were the main caregiver of more than 1 person in a situation of dependency, or had modified legal capacity.

Figure 1 shows visually the study flowchart described above.

**Figure 1. F1:**
[figure not shown]
Study flowchart.

### Sample Size

To determine the necessary sample size for this study, the G*Power software was used. Based on similar studies and assuming that caregivers’ QoL is the primary outcome of this study (with all other variables treated as secondary and/or exploratory outcomes), power analysis was performed [39]. An a priori power analysis was conducted using a paired t test on the primary outcome, as an improvement in informal caregivers’ QoL was expected after the intervention. A moderate effect size (Cohen *d*=0.5), a significance level of .05, and a statistical power of 80% (1−*β*=.80) were assumed. Under these assumptions, a sample of 54 caregivers who complete the study (*df*=53) provides power greater than 80% to detect the expected effect.

Given the multiplicity of the planned analyses, confirmatory inference will be restricted to the primary outcome. Secondary and exploratory outcomes will be interpreted with caution, without applying a formal adjustment for multiple comparisons, and emphasis will be placed on effect sizes and their 95% CIs.

In addition, an attrition rate of up to 20% is anticipated (due to dropouts, absence from the postintervention assessment, or technical problems with the wearable device or platform). Therefore, we plan to recruit approximately 65 informal caregivers, so that at least 54 are expected to complete the study and be included in the primary analysis.

### Ethical Considerations

The project complies with the fundamental principles for research with human beings established in the Declaration of Helsinki, the Oviedo Bioethics Convention, and the Universal Declaration on the Human Genome and Human Rights.

The performance of this study will respect the applicable regulations of ethics regarding research with humans. Also, for data protection, we will follow the Regulation (EU) 2016/679 of the European Parliament and of the Council of April 27, 2016, on the protection of natural persons regarding the processing of personal data and on the free movement of such data and the national regulations on data protection.

To guarantee these aspects, the research protocol was submitted to the Ethics Committee for Research and Teaching of the Universidade da Coruña. A favorable report from this committee was obtained (2023_019).

The group of participants in the study will be adults in an informal caregiver’s role. Participation in this project will not implicate any risk or damage to the participants, who will (1) cover baseline, mid-term, and end-line surveys, (2) wear a noninvasive wearable device for the duration of the validation, (3) interact and use the platform, and (4) participate in individual semistructured interviews.

Particular attention will be paid to ethical issues: aspects that guarantee data protection and informed and voluntary participation.

The research group is committed to guaranteeing the confidentiality and protection of the data obtained from the participants in the project. The data of the participants will be collected in a pseudonymized form to allow validation tests at different stages of the development process. The interviews will be audio-recorded, with the consent of the participants. A transcript of the interviews will then be made, and the identities of the participants will be coded. The information that might allow identification shall be anonymized. Subsequently, the audios will be deleted.

The access to the identification of the participants will be exclusively carried out by the research team. Once the study has been completed, any possibility of participant identification will be eliminated.

The platform’s cybersecurity mechanisms will be identified and implemented following current legislation.

Participation will be completely voluntary, and informed consent will be obtained from each person. For this purpose, detailed information sheets and an informed consent form will be provided to explain the participation in the study. There is no obligation to complete the experiment, so participants can withdraw from it at any time.

Individual participant data will be available for sharing with the scientific community, upon request and after the acceptance for publication of the main findings from the final data set.

The data will be completely anonymized for sharing. The dataset will include only the results of quantitative variables.

Finally, for validation testing of the platform, it will be necessary to obtain a robust prototype. This prototype will be previously tested by professionals of the team to ensure the absence of unexpected behaviors of the application that may generate discomfort to participants.

The cost of the Xiaomi Mi Band 7 wristbands will be supported by the project team, and people will have to authorize the capture of data from this device (physical activity and sleep).

Participants will not receive monetary compensation. As compensation for their time, participants will receive the Xiaomi Mi Band 7 wristband used in the study at no cost (ie, they may keep the device after participation). Compensation is not contingent on completing all study procedures; participants may withdraw at any time without penalty.

### Intervention

The intervention lasts 3 months and is based on the use of *CuidaconTIC* and the Xiaomi Smart Band 7 activity wristband. Participants will regularly use *CuidaconTIC* services and wear the Xiaomi Smart Band 7 wristband.

*CuidaconTIC* is a technological platform for caregivers developed through the TechQoL4Carers project [34]. The research team designed and developed *CuidaconTIC* through an iterative and participatory process with informal caregivers, the platform’s end users, and other actors involved in care, such as health science professionals.

The platform is integrated into both a website and a mobile application. The services offered include a summary of the individual’s health status, training content, advice, and personalized recommendations based on their QoL, care situation, occupational balance, self-management of health, and empowerment. It also allows for synchronization with the Xiaomi Smart Band 7 activity wristband. *CuidaconTIC*, 1.0 version, will be used for the pilot project. After the trial results are integrated, the final version of the platform will be obtained. The main services of the *CuidaconTIC* platform are: My daily summary, My health, My week, I take care of myself, and I take care of you.

Caregivers are expected to access and use the TechQoL4Carers platform at least once a week to complete the weekly questionnaire and consult the training content related to self-care and care provision at least once a month.

The research team will provide caregivers with the Xiaomi Smart Band 7 wristband to capture health-related data and synchronize it with the platform. Participants are expected to use the wristband daily during the 3-month intervention. These data will be combined with other information collected through subjective measurements to provide personalized content and recommendations.

### Outcomes and Measurements

Participants will complete the quantitative evaluations at 3 points in time: baseline (t_0_), intermediate (t_2_), and final (t_4_) through the *CuidaconTIC* platform in its evaluation section. For the final assessment, people may participate in a semistructured interview. The evaluations at these time points will be face-to-face at the reference centers or, if preferred, at the facilities of the research center.

The weekly evaluation will be performed through the *CuidaconTIC* platform and will be reminded through notifications in the mobile application.

The schedule of enrollment, interventions, and assessments, based on the proposal of the SPIRIT statement [36], can be consulted in Table 1.

**Table 1. T1:** Schedule of enrollment, interventions, and assessments.

	Enrollment	Preassessment	Intervention (3 mo)			Postassessment
	–t_1_	t_0_ (baseline)	t_1_^a^	t_2_^b^	t_3_^c^	t_4 _(post intervention)^d^
Enrollment						
Informed consent	✓					
Configuration						
Wristband delivery	✓					
*CuidaconTIC* settings	✓					
Intervention						
*CuidaconTIC* platform						
Xiaomi Band 7						
Assessments						
EQ-5D-5L		✓		✓		✓
CarerQoL^e^		✓		✓		✓
ZBI^f^		✓		✓		✓
CBI^g^		✓		✓		✓
OBQ-E^h^		✓		✓		✓
PEI^i^		✓		✓		✓
Physical activity						
Sleep						
My week-Q^j^						
Satisfaction-Q^k^						✓
SUS^l^						✓
Interview						✓

a t_1_: 6 weeks of intervention (1-6 wk).

b t_2_: mid-term assessment.

c t_3_: 6 weeks of intervention (7-12 wk).

d t_4_: 1-month post intervention.

e CarerQoL: Care-Related Quality of Life.

f ZBI: Zarit Burden Interview.

g CBI: Caregiver Strain Index.

h OBQ-E: Occupational Balance Questionnaire-Spanish version.

i PEI: Psychological Empowerment Instrument.

j My week-Q: *CuidaconTIC* weekly Questionnaire.

k Satisfaction-Q: *CuidaconTIC* Satisfaction Questionnaire.

l SUS: System Usability Scale.

### Characteristics of Participants

#### Sociodemographic Questionnaire

A sociodemographic questionnaire was developed with the following variables: age, gender, marital status, educational level, residential environment, household unit, employment situation, years in the role of caregiver, supports, type of support, relationship with the person receiving care, main difficulties, diagnosis, and age of the cared-for person.

#### Primary Outcome Measures

##### EQ-5D-5L

EQ-5D-5L is a self-administered scale to assess perceived health-related QoL [40-42].

Health state is obtained from the EQ-5D-5L, through its descriptive system with 5 dimensions: mobility, self-care, usual activities, pain/discomfort, and anxiety/depression. The dimensions are scored on a 5-point Likert scale reflecting the level of severity (no problem, slight problems, moderate problems, severe problems, and extreme problems or unable to perform). The health profile or health state describes the level of severity that the person perceives in each dimension and it is represented through an individual code for each dimension scored between 1 and 5 or through a single 5-digit code (ranging from 11111 to 55555).

Overall health is derived from a visual analog scale (EQ-VAS) on perceived health, from 0 to 100. In this way, the person scores his or her health on a given day, assigning it a value between 0 (the worst health you can imagine) and 100 (the best health you can imagine).

##### Care-Related Quality of Life Instrument

Care-related quality of life (CarerQoL) is a self-administered instrument to measure care-related QoL and the impact of the care on caregivers [43].

CarerQoL will be measured through 5 negative and 2 positive dimensions (CarerQoL-7D). The 7 dimensions are fulfillment from caregiving, relational problems, mental health problems, problems with combining daily activities with care, financial issues, perceived support, and physical health problems [44]. They are scored on a Likert scale with 3 values indicating the severity level (no, some, and a lot). For negative dimensions, the values are 0 (a lot), 1 (some), and 2 (no); while for positive dimensions, the values are reversed 0 (no), 1 (some), and 2 (a lot). Score range: 0 to 14. A tariff for the CarerQoL based on Dutch preferences is also available which allows a weighted sum score, ranging from 0 to 100 [44,45]. The higher the score on the dimensions, the better the situation of care.

The CarerQoL-VAS allows rating how happy the person feels at that moment as a measure of general well-being. This construct is scored on a horizontal VAS range from 0 (completely unhappy) to 10 (completely happy). The higher the score, the better the situation in terms of well-being.

### Secondary Outcome Measures

#### Zarit Burden Interview

Zarit Burden Interview is a questionnaire designed for the caregiver population to assess the level of burden and detect possible caregiving stressors [46-49]. The 22-item version is used, scored from 1 to 5.

The score range is 22 to 110. Score interpretation is as follows, with 2 cut-off points: no burden, 22 to 46 points; mild burden, 47 to 55 points; and severe burden, 56 to 110 points.

#### Caregiver Strain Index

The Caregiver Strain Index or Robinson Index is a 13-item tool for caregivers to measure perceived strain, and detect burden, and possible stressors related to care [50-52]. Each item is answered in a dichotomous way: yes or no.

The score range is 0 to 13. Scores of 7 or more identify caregivers at risk for high caregiving strain or burden.

#### Occupational Balance Questionnaire, Spanish Version

Occupational balance will be measured through Occupational Balance Questionnaire-Spanish version [53,54]. This self-administered tool of 13 items is scored on a 6-step ordinal scale, ranging from 0 (completely disagree) to 5 (completely agree). It evaluates the person’s current experience with occupational balance, considering the quantity, variability, and meaning attributed to activities of daily living.

The score range is 0 to 65. The results show that the higher the score, the higher the occupational balance.

#### Psychological Empowerment Instrument

The Psychological Empowerment Instrument adapted will be used to assess changes in informal caregivers’ perceptions of empowerment.

It is a self-administered instrument that measures psychological empowerment in the work environment, considering 4 cognitive dimensions: competence, meaning, self-determination, and impact [55,56]. The Spanish version of the Psychological Empowerment Instrument comprises 13 items divided among the 4 dimensions and scored on a 7-point Likert scale [57]. This version will be used in the study replacing the references to work and the role of the workers with terms associated with care and caregivers.

The score range is 7 to 91 points. The higher the score, the higher the level of psychological empowerment.

#### Activity Wristband: Xiaomi Smart Band

In the study, participants will use the Xiaomi Smart Band [58] activity wristband regularly during the 3 months of the intervention.

Version 7 of the Xiaomi Smart Band activity wristband allows the recording and monitoring of health-related variables: physical activity, sleep, heart rate, blood oxygen saturation (SpO₂), women’s health, and stress [58].

The wristband will be automatically synchronized with the TechQoL4Carers platform. The variables that will be monitored during the project are: physical activity (number of steps, distance in meters, and activity in min) and sleep (light sleep, deep sleep, rapid eye movement sleep, and time awake after sleep onset in min).

#### My Week Questionnaire

My Week Questionnaire is a questionnaire designed by the research team included on *CuidaconTIC*. Participants could self-administer it weekly to identify changes perceived in daily functioning based on the variables studied: QoL, impact of the care, occupational balance, self-management of health, and empowerment.

The development of this questionnaire has been based on previous surveys developed by the research team [59], but it has been adapted to caregivers for this study.

My Week Questionnaire is integrated with 9 items that are answered using a 6-point Likert scale, ranging from 0 (completely disagree) to 5 (completely agree). The score range is 0 to 45 points. The higher the score, the greater the perception of positive changes in QoL-related factors.

#### *CuidaconTIC* Satisfaction Questionnaire

The *CuidaconTIC* Satisfaction Questionnaire will be administered at the end of the intervention to assess end-user satisfaction with the project and the technology. The questionnaire has been adapted for this study based on the Technology Satisfaction Factor Loadings questionnaire [60].

It is a self-administered questionnaire consisting of 16 items grouped into 4 factors (competence, assessment, performance, and TechQoL4Carers platform), rated on a 6-point scale, ranging from 0 (completely disagree) to 5 (completely agree). The score range is 0 to 80. The higher the agreement with the statements, the higher the satisfaction with the project.

#### System Usability Scale

The System Usability Scale is a tool used to measure subjective perceptions of technology usability [61]. It contains 10 items scored on a 5-point Likert scale, from 0 (strongly disagree) to 4 (strongly agree). The items are statements about the effectiveness, efficiency, and satisfaction with a system or product.

The score range is 0‐100. The higher the score, the higher the perceived level of usability of a product or system. Scores of 70 or more identify acceptable products [62] with a good (70-85) and excellent (85 or more) level of usability.

#### Semistructured Interview

At the end of the project, a semistructured individual interview will be conducted with each caregiver. The interview guide has been designed to elicit the meaning that the caregivers give to the caregiving experience, to the participation in the project, to the use of technology in the project, and the impact of this project on their daily life (QoL, impact of care, occupational balance, self-management of health, and empowerment).

This interview will take place in the collaborating entities, in a quiet and comfortable place, and at a time that suits the needs of the participants. It will be recorded with a digital device to facilitate the literal transcription. This information will be coded and at the end of the study, the transcriptions will be anonymized and the audio will be deleted.

The interview guide can be found in Appendix B in Multimedia Appendix 2.

### Analysis

The statistical analysis of the data will be performed using R software (version 4.4.3 [63]). All data will be cleaned and processed prior to analysis, and a range of statistical procedures will be performed based on the study hypotheses and objectives. The significance level for hypothesis testing is set at 5%. Numerical variables will be presented as mean and SD, along with range, minimum, and maximum values, while categorical variables will be presented as absolute frequency and valid percentage.

After performing a descriptive analysis of the variables, we will determine the distribution of the data using formal tests of normality: the Kolmogorov-Smirnov or Shapiro-Wilk tests, as appropriate. This will help decide whether parametric or nonparametric statistical methods are used. Parametric tests, such as the paired *t* test, ANOVA, and Pearson correlation, will be used to analyze data if normality is confirmed. Otherwise, nonparametric tests, including the Wilcoxon signed-rank test, Friedman and Spearman rank correlation, will be employed. Pre- and postintervention changes in the primary outcome and in the other continuous variables will be analyzed using a paired Student *t* test or, where appropriate, the Wilcoxon signed-rank test. The effect size of within-subject changes will be estimated using Cohen *d*, in order to quantify the magnitude of the observed changes. In addition, 95% CIs for these effect sizes will be reported. It is important to note that QoL, considered the primary outcome of the study, will be used for formal confirmatory inference to control the type I error rate; analyses of other outcomes will be considered secondary or exploratory.

In addition, exploratory correlation analyses will be conducted to examine relationships both among the different outcomes from the tools and between these outcomes and summary measures of the biometrical parameters recorded by the wearable devices. Depending on the distribution of the variables, Pearson or Spearman correlation coefficients will be used. For these analyses, the correlation coefficient r and its 95% CI will be reported as the primary measure of effect size. To explore relationships between categorical variables, the chi-square test will be applied. When expected cell frequencies are low, the Fisher exact test will be used instead.

Furthermore, given the longitudinal nature of the study, data from wearable devices and scores from the weekly questionnaire will be summarized at the weekly level. For wearable data, daily recordings will be checked for validity and aggregated as weekly averages. Based on previous studies [64,65], a week will be considered valid if it contains at least 4 days with usable recordings. Trends in weekly measurements of sleep, heart rate, and step count, as well as weekly questionnaire scores, will be analyzed using repeated-measures ANOVA or the nonparametric Friedman test, depending on data distribution, including only participants who meet prespecified minimum completeness criteria for the weekly data.

To handle incomplete weekly or wearable data systematically and reduce the risk of biased estimates, the amount and pattern of missing wearable and weekly questionnaire data will be described, and all available valid weeks will be included in the analyses under a missing-at-random assumption. In addition, sensitivity analyses will be performed to assess the robustness of the longitudinal and correlational findings to different assumptions about missing data.

Regarding the qualitative analysis of the final interview, the instructions of the thematic analysis by Braun and Clarke [66] will be followed, who defined 6 phases: (1) familiarizing with the data; (2) generating initial codes; (3) searching for themes; (4) reviewing themes; (5) defining and naming themes; and (6) producing the report. The analysis will be carried out independently by 3 researchers using the previously described inductive approach, and MAXQDA 24 software [67] will be used for the triangulation of the information.

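### For pre-post changes the only stated effect estimate is Cohen d with a 95% CI, kept even when the test switches to Wilcoxon, and no CI in scale points is stated

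*Protocol article*

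**What the plan says.** The Analysis section of the protocol article applies formal normality tests and states of their result: "This will help decide whether parametric or nonparametric statistical methods are used". Changes from before to after the intervention, in the primary outcome and the other continuous variables, "will be analyzed using a paired Student *t* test or, where appropriate, the Wilcoxon signed-rank test".

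The effect estimate carries no such condition: "The effect size of within-subject changes will be estimated using Cohen" *d*, and "95% CIs for these effect sizes will be reported". The section names no estimate belonging to the Wilcoxon branch and no CI for the change in scale points. Means and SDs appear as descriptive summaries. The correlation coefficient with its CI is named as an effect measure, but only for the correlation analyses.

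The Sample Size section restricts confirmatory inference to the primary outcome, quality of life. Secondary and exploratory outcomes get no multiplicity adjustment, and for them "emphasis will be placed on effect sizes and their 95% CIs".

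**The concern.** The test depends on the distribution of the changes, but the estimate does not. Three consequences follow.

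- **Mismatch.** Wilcoxon responds to the ranks of the changes and is centred on their pseudo-median. Cohen d is a mean divided by an SD. With skewed changes the two can point to different conclusions in the same table row.
- **Interval.** The usual CI for d rests on normal differences. The Wilcoxon branch is entered because normality was rejected.
- **Scale.** If d is standardised by the SD of changes, which is the d that drives a paired t test, the same gain looks small on a tool with low pre-post correlation and large on one with high correlation. The tools have very different ranges (EQ-VAS 0 to 100, Zarit 22 to 110, Caregiver Strain Index 0 to 13, Occupational Balance Questionnaire 0 to 65), so readers will be tempted to compare them through d.

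At stake is how the results for burden, strain, occupational balance and empowerment are read, since the plan points readers to these effect sizes and intervals.

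**Working it through.** **Inputs.** From the Sample Size section: 54 completers, d = 0.5, significance level .05, paired t test. Assumed, because the article does not give them: the shape of the changes, the pre-post correlation r, equal SDs at both visits, and a noncentral-t CI for d.

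**1. The plan's own figure.** Paired-t power with df = 53 and noncentrality 0.5 × √54 = 3.67 is 95.0% two-sided and 97.6% one-sided. The statement that 54 gives more than 80% power is correct. In this calculation d is the mean change divided by the SD of changes.

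**2. Estimate against test.** Changes were drawn from an exponential distribution shifted to mean zero, so true d = 0, with n = 54 and 3,000 samples.

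- The pseudo-median is -0.16 SD.
- Wilcoxon was significant in 22.8% of samples and the t test in 6.7%.
- In at least 22.8 - 6.7 = 16.1% of samples, Wilcoxon was therefore significant while the t test was not. A non-significant t test at n = 54 means |d| below t(0.975, 53)/√54 = 0.273 and a normal-theory CI for d that includes 0.

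This is not a false-positive rate for Wilcoxon, because these changes are not symmetric about zero. It shows that the test and the reported estimate answer different questions.

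**3. Coverage of a noncentral-t 95% CI for d.** True d = 0.5, n = 54, 10,000 samples per shape. The Shapiro-Wilk column uses the first 3,000.

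| Shape of changes | CI for d, all samples | CI for d, Shapiro-Wilk rejects | t interval for mean change |
|---|---|---|---|
| Normal | 94.8% | 96.3% | 95.3% |
| Laplace | 93.4% | 93.8% | 95.0% |
| t, 5 df | 93.2% | 92.9% | 95.1% |
| t, 3 df | 87.0% | 89.2% | 95.2% |
| Gamma, skewness +1 | 98.3% | 98.5% | 94.4% |
| Gamma, skewness -1 | 89.0% | 90.3% | 94.5% |
| Exponential, skewness +2 | 99.6% | 99.5% | 93.6% |
| Exponential, skewness -2 | 81.0% | 81.2% | 93.2% |
| Lognormal | 98.8% | 98.7% | 90.1% |

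The interval for d is off in both directions under marked skew and too narrow under heavy tails. It is near nominal for mild departures. The interval for the mean change stays within 93% to 95% except for the lognormal.

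**4. Dependence on the pre-post correlation.** With equal SDs, d = Δ / (SD × √(2(1 - r))). For a gain Δ of 0.3 SD:

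- r = 0.3: 0.3 / √1.4 = 0.25
- r = 0.7: 0.3 / √0.6 = 0.39
- r = 0.9: 0.3 / √0.2 = 0.67

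Standardised by the baseline SD, the value is 0.30 throughout. In points, an assumed EQ-VAS gain of 5 with SD 20 gives d = 0.21, 0.25, 0.32, 0.40 and 0.56 at r = 0.3, 0.5, 0.7, 0.8 and 0.9, against 0.25 throughout with the visit SD.

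**5. Effect of the fix on N.** None. If every test went to Wilcoxon, two-sided power at 54 and d = 0.5 would be about 94% (relative efficiency 0.955) or 92% (lower bound 0.864).

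**The case against.** The strongest reply is that much of the harm depends on details the article leaves open. It names neither the CI method nor the standardiser of d, and a condensed article may leave both to the full plan. That stands. A reader might infer that the CIs are wrong whenever Wilcoxon is used, but the documents do not support this. The table shows near-nominal coverage for mild departures. A further simulation with bounded, discrete scores resembling these tools (n = 54, assumed latent correlation 0.5 to 0.7, d about 0.34 to 0.56, 6,000 samples each) gave 93.9% to 96.9% among samples in which Shapiro-Wilk rejected. Likewise, the dependence on r disappears if d is divided by the baseline SD, which the article's wording permits.

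Other tempting readings also go too far:

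- That d does not measure the size of a change. It does, in standardised form; it does not give points.
- That the change in points stays unknown. Means are to be reported, and for the same participants the difference of the baseline and final means is the mean change. Only its CI is missing.
- That these CIs stand in for multiplicity control. Type I error is handled by confining confirmatory inference to quality of life, and no error guarantee rests on the CIs.
- That a bootstrap CI for d would cure the problem. A percentile bootstrap of the mean-to-SD-of-changes ratio covered 85% for t with 3 df and 75% for the lognormal (800 samples each).

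The reply does not remove the central point. The article does not leave the estimator open: it names one for all within-subject changes and makes only the test conditional on normality.

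**Conclusion.** The point holds as a weakness in the stated estimator, not as an error that invalidates the trial. For pre-post change, Cohen d with a CI is the only effect estimate named. It does not match the test in the Wilcoxon branch, and the change in scale points has no stated CI.

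Under strong skew the mismatch is material: in the example at least 16% of samples combine a significant Wilcoxon test with a d whose normal-theory CI includes 0. A normal-theory CI for d, if used, may cover anywhere from 81% to 99.6% under marked skew or heavy tails, and close to 95% under mild departures. If d uses the SD of changes, one and the same gain can read as 0.25 or 0.67 depending on r, so d values are not directly comparable across tools.

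These sizes rest on assumed shapes and correlations. The consequence is confined to how magnitudes are read, mainly for secondary and exploratory outcomes. The confirmatory test on quality of life is unaffected.

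**What to change.** In the Analysis section:

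1. Make the mean change in scale points with its 95% CI the lead estimate for every pre-post outcome.
2. Wherever Wilcoxon is used, add the Hodges-Lehmann shift with its CI. Under skew it may differ from the mean change, and showing both makes this visible.
3. Keep Cohen d only as a supplement, standardised by the baseline SD, and name its CI method.

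In the Sample Size section, refer the sentence on emphasis to the estimates in items 1 and 2.

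The cost is a few lines of wording and standard R output, with no new data and no change to the sample size. The article says it was submitted before analysis, so the change could still be fixed in advance.
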